# Efficacy and safety of heart rate control with esmolol on the incidence and duration of organ failure in predicted severe acute pancreatitis: protocol of a multicenter, open-label, randomized controlled trial

**DOI:** 10.3389/fmed.2025.1642721

**Published:** 2025-07-30

**Keywords:** acute pancreatitis, *β*-blockers, esmolol, heart rate, organ function

## Abstract

**Introduction:**

Overactivation of the sympathetic nerve system can lead to a sustained increase in heart rate, which may impair blood perfusion and organ function. Previous studies have demonstrated that the use of *β*-blockers like esmolol can reduce heart rate, thereby improving clinical outcomes in patients with septic shock. For acute pancreatitis (AP), which shares a similar inflammatory pathophysiology with sepsis, previous experimental and observational studies showed significant sympathetic excitation during the acute phase, and the use of *β*-blockers might be clinically beneficial. This study aims to test the hypothesis that early intravenous esmolol administration to control heart rate will improve the incidence and duration of organ failure in patients with predicted severe acute pancreatitis (pSAP).

**Methods:**

This is an investigator-initiated, multicenter, open-label, randomized controlled trial. All patients with pSAP who still exhibit elevated heart rate (≥110 bpm) after 6 h of adequate intravenous fluid resuscitation within the first 72 h of symptom onset will be screened for eligibility. A total of 146 participants will be randomized to receive either esmolol or standard care. Patients in the esmolol group will receive a continuous esmolol infusion to maintain a heart rate between 80 and 94 beats per minute (bpm) within the first 96 h of randomization. The primary endpoint is organ failure free and alive days (OFFDs) to day 14 after trial entry. Secondary endpoints are comprised of both process and clinical measures, including heart rate variability, the proportion of patients’ heart rate recovered to <95 bpm, changes in plasma interleukin-6 and C-reactive protein between day 1 and day 5, in hospital and 90-day mortality, new-onset organ failure, free and alive days to day 30 for intensive care admission, and requirement of mechanical ventilation, vasopressor use, and renal replacement therapy.

**Discussion:**

This study will provide top-class evidence concerning the effects of heart rate control with a classic *β*-blocker on the incidence and duration of organ failure in patients with pSAP and increased heart rate.

**Ethics and dissemination:**

This study has been approved by the ethics committee of Jinling Hospital, Nanjing University (2022DZKY-076-02) and all participating sites. Results will be disseminated through peer-reviewed journals and scientific conferences.

**Trial registration:**

Identifier, ChiCTR2400080160.

## Introduction

Acute pancreatitis (AP) is a systemic inflammatory disease with significant morbidity, and about 20% of patients, who have more intense inflammation, develop severe AP (SAP) (1, 2). The inflammatory response, combined with intense stress and pain, leads to elevated sympathetic activation in SAP patients (3). In turn, the persistent excitation of the sympathetic nervous system can reciprocally intensify inflammation, triggering the release of inflammatory mediators and perpetuating a vicious cycle (4).

Given that sympathetic activation is a hallmark of inflammatory diseases (5, 6), numerous efforts have been undertaken to modulate its activity in the hope of improving clinical outcomes (7, 8). Recent studies suggest that modulating sympathetic nerve activity using *β*-1 adrenergic blockers may offer therapeutic benefits in sepsis by attenuating excessive inflammatory responses and organ failure (6, 9). Esmolol, a short-acting intravenous *β*-blocker, was previously used to treat inflammatory conditions like sepsis (10, 11). It works by inhibiting the effects of adrenaline on sympathetic overactivation, thereby reducing heart rate to improve tissue perfusion and suppressing inflammatory mediators (12).

A phase II clinical trial involving 154 patients with septic shock demonstrated that esmolol could reduce heart rate without affecting mean arterial pressure (13). Notably, esmolol significantly reduced 28-day mortality (49.4% in the esmolol group vs. 80.5% in the control group, *p* < 0.001) (13). Another study in 2015 found that combining milrinone and esmolol improved cardiac function and 28-day survival in patients with severe sepsis (14). Recently, two large-scale trials were published testing the effects of a new ultra-short-acting *β*-blocker, landiolol, in patients with septic shock and persistent tachycardia [The Landi-SEP (15) and STRESS-L (16)]. The former found that landiolol was effective in reducing and maintaining heart rate without increasing vasopressor requirements after 24 h. However, the latter was halted prematurely after enrolling only 37% of the planned participants. The decision was made due to the lack of evidence suggesting that landiolol could improve organ function, coupled with indications of potential mortality harm. The most likely explanation, as the authors suggested, may be compromised cardiac output in patients with already existing shock.

From the pathophysiological perspective, elevated heart rate and cardiac output typically occur during the acute phase of AP, primarily mediated through systemic inflammatory activation, which is associated with excitation of the sympathetic nervous system (17). Our previous study showed that elevated sympathetic activity was strongly associated with a poor prognosis (3). Interventions such as electroacupuncture, which stimulate the vagus nerve and, in turn, reduce sympathetic nervous system activity, have been shown to reduce pancreatic injury in AP mice (18). However, based on observations in sepsis trials, it is also possible that the use of *β*-blockers may reduce cardiac output, thereby compromising tissue perfusion. Taken together, due to the lack of controlled trials, the efficacy and safety of early heart rate control with *β*-1 adrenergic blockers on outcomes in AP patients, particularly those at high risk of SAP, remains unclear. This trial aims to evaluate whether early intravenous esmolol administration to control heart rate can reduce the incidence and duration of organ failure in patients with predicted severe acute pancreatitis (pSAP).

## Methods and analysis

### Aim and objectives

The *β*-Blocker esmolol on the evolutioN of organ faIlure in aCute pancrEatitis (BeNICE) trial aims to assess the effect of early heart rate control with intravenous esmolol on the incidence and duration of organ failure in patients with pSAP.

### Study design

This investigator-initiated, multicenter, open-label, randomized controlled trial will be conducted among 8 to 10 participating sites over 12–24 months. The trial is registered at the Chinese Clinical Trials Registry (ChiCTR2400080160).

### Trial committees

The Trial Management Committee (TMC), comprising primary investigators, co-investigators, and members of the Chinese Acute Pancreatitis Clinical Trials Group (CAPCTG), will oversee the trial’s daily operations. An expert clinical panel from CAPCTG will provide governance and audit the study. A writing and publication committee will draft and submit the manuscript to academic journals and determine authorship.

### Study population

Adult patients diagnosed with AP, admitted to participating sites, will be assessed for eligibility. After obtaining informed consent, eligible participants will be randomized.

### Eligibility criteria

The inclusion and exclusion criteria are as follows:

*Inclusion criteria:*

Diagnosis of acute pancreatitis (2): symptoms and signs of AP based on abdominal pain, serum amylase at least three times the upper limit of the normal range, and/or characteristic findings on computed tomography;Within 72 h of symptom onset;Predicted severe acute pancreatitis, based on APACHE-II score≥8 or CRP > 150 mg/L (19);Heart rate ≥110 bpm sustained for ≥10 min after at least 6 h of adequate intravenous fluid resuscitation;Age ≥18 years;Written informed consent from the patient or next of kin;

The treating physician should make sure that adequate fluid resuscitation has been delivered before initiation of the trial intervention. Adequate fluid resuscitation should be achieved using repeated fluid challenges based on current guidelines (20). Potential targets include any or all of the following based on the clinical setting of the study site: (1) Mean arterial pressure between 65–85 mmHg, (2) Good peripheral perfusion on clinical examination, e.g., urinary output > 0.5 mL/kg/h, blood lactate < 2 mmol/L, (3) Other measures of cardiac output/flow, e.g., cardiac output, stroke volume variability, (4) Central venous pressure ≥8 mmHg, (5) Biochemical targets of hematocrit 35–44%.

*Exclusion criteria:*

Patients who had received *β*-blocker therapy before enrollment during the index admission;Patients with chronic cardiac dysfunction (New York Heart Association Classification III or above);Pregnancy;Active bronchial asthma or history of asthma;Severe chronic obstructive pulmonary disease requiring home oxygen therapy;Predicted death within 24 h;Patients with contraindications to *β*-blockers (e.g., severe bradycardia, advanced heart block, cardiogenic shock, untreated pheochromocytoma).

### Randomization and blinding methods

Permuted block randomization (variable block size = 4 or 6), stratified by site, will be performed using a computer-generated list via the Interactive Web Response System (IWRS). The study is open-label, but laboratory personnel and data analysts will be blinded to the allocation sequence.

### Sample size, centers, and recruitment

Based on previous large studies [the CLEVER-AP (21) and the PERFORM (22)] conducted by the CAPCTG, the mean organ failure free and alive days (OFFDs) to 14 days in patients with pSAP was estimated as 7.3 (SD 4.1). Both of the two studies were large-scale ones conducted across China in similar population. The former aimed to compare the effect of a balanced solution versus normal saline fluid therapy in patients with pSAP. The latter was a long-running prospective cohort study collecting patients with hypertriglyceridemia-associated acute pancreatitis. Per the standard formula calculated with PASS (ver.15.0; NCSS, LLC),^1^ a sample size of 66 patients per group provides 80% power to detect a two-day difference in OFFDs between groups, which is thought to be the minimum clinically meaningful treatment effect. After accounting for a 10% loss of follow-up, 146 patients (73 per group) are planned to be randomized.

The first patient was recruited on Feb 8th, 2024, and the planned finishing date is Dec 31st, 2025. The follow-up will be finished after the 90-day follow-up of the last recruited patient is completed.

### Study interventions

The study protocol only determines whether or not to use esmolol.

Group 1: Esmolol group

Patients will receive esmolol infusion within 1 h of randomization, starting at 25 mg/h, titrated to maintain a heart rate of 80–94 bpm, with a maximum dose of 0.2 mg/kg/min. The infusion will continue for 96 h unless: (1) the heart rate decreases below 80 bpm and re-evaluation needs to be performed after 20 min; (2) systolic blood pressure falls below 90 mmHg; (3) severe arrhythmias develop; or (4) the clinician deems it necessary based on the patient’s condition.

Meanwhile, we will implement stringent measures to mitigate the risk of low cardiac output in the study patients, including: (1) adequate fluid resuscitation prior to esmolol initiation; (2) patients assigned to the esmolol group had their blood pressure monitored every 15 min. and (3) cardiac output monitoring when necessary, using techniques like echocardiography, invasive hemodynamic monitoring, etc., as judged by the treating physicians.

Group 2: Standard care group

Patients will receive standard care without a placebo at the discretion of the treating physicians.

### Management of acute pancreatitis

Apart from the trial intervention, all the study patients will be managed by the local clinical team at each participating site based on international guidelines (20, 23), including adequate fluid resuscitation, early enteral nutrition (start within 48 h after admission), routine medical treatment (antibiotics and sedatives as needed, organ support like mechanical ventilation, renal replacement treatment (RRT), and vasopressors commenced at the discretion of the treating team), etc. Infected pancreatic necrosis will be managed using a step-up approach, either surgically or endoscopically, depending on the technical preference of the local team (20, 24).

### Endpoints

#### Primary endpoint

The primary endpoint is organ failure free and alive days (OFFDs) to 14 days of enrollment, defined as the number of days alive without failure of the respiratory, renal, or cardiovascular system (25). An individual sequential organ failure assessment (SOFA) score of two or more was defined as organ failure (26). Patients discharged from the hospital prior to day 14 were considered alive and free from organ failure from the day of discharge onward. For patients who died before day 14, OFFDs were assigned a value of zero. If patients are readmitted to the index study site with recurrent organ failure within 14 days, only the last period alive and free of organ failure will be counted.

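### The primary endpoint credits days after discharge as free of organ failure with no condition on organ status at discharge, and does not say that a death after discharge takes precedence

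*Protocol article*

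**What the plan says.** The Primary endpoint section of the protocol article fixes the scoring in five steps.

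- The endpoint is "defined as the number of days alive without failure of the respiratory, renal, or cardiovascular system", counted to 14 days.
- The threshold for failure is: "An individual sequential organ failure assessment (SOFA) score of two or more was defined as organ failure".
- For discharge: "Patients discharged from the hospital prior to day 14 were considered alive and free from organ failure from the day of discharge onward".
- For death: "For patients who died before day 14, OFFDs were assigned a value of zero".
- For readmission, the count is cut back to the final failure-free stretch: "If patients are readmitted to the index study site with recurrent organ failure within 14 days, only the last period alive and free of organ" (quotation cut short here).

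The discharge sentence sets no condition on SOFA score, organ support, reason for leaving or destination. The death sentence sets no limit on place of death. Neither says which prevails when both apply. The readmission sentence covers the index site only.

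Elsewhere, the abstract lists "in hospital and 90-day mortality" among the secondary endpoints. The section on sample size and recruitment adds: "The follow-up will be finished after the 90-day follow-up of the last recruited patient is completed". Vital status at day 14 should therefore be known for discharged patients. The randomization section says: "The study is open-label, but laboratory personnel and data analysts will be blinded to the allocation sequence".

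**The concern.** The discharge sentence replaces observation with an assumption. That is reasonable for a patient who goes home recovered. It is not reasonable for one who leaves while still meeting the article's own definition of organ failure. Such a patient contributes no failure-free days under the definition but gets every remaining day under the discharge sentence. A bad outcome is scored as a good one.

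Two features make this matter for the primary comparison. First, discharge is decided by clinicians who know the allocation, so the share of such patients could differ between arms, in either direction. Second, the planned missing-data safeguard would not detect the problem. Under Statistical analysis, sensitivity analyses start only if more than 5% of primary outcomes are missing. Days filled in by the discharge rule count as observed, so they never reach that trigger.

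A smaller issue is a patient who dies after discharge and before day 14. One sentence treats the patient as alive, the next assigns zero, and a programmer has to choose.

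**Working it through.** **Inputs.** Mean OFFDs 7.3, SD 4.1, target difference 2 days, 80% power, 66 per group, 10% loss and 73 per group come from the section on sample size and recruitment. Two-sided 0.05 comes from Statistical analysis. The scoring rules come from Primary endpoint. The documents give no rate of discharge with organ failure, transfer or death after discharge, so all frequencies below are assumptions.

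**Step 1: the plan's own figure.** n per group = 2 × (1.960 + 0.8416)² × 4.1² / 2² = 2 × 7.849 × 16.81 / 4 = 65.97, so 66, with power 0.800. Adding 10%: 66 × 1.10 = 72.6, so 73 per group and 146 in total. The stated figures are reproduced, so 2 days and 73 per arm serve as yardsticks.

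**Step 2: the rules applied to example patients.** The credit after discharge on day d is taken as 14 − d (15 − d if the day of discharge is itself counted).

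| Example | Discharge sentence alone | Other text in the section |
|---|---|---|
| A. Leaves on day 5 with SOFA ≥2; failure persists, alive at day 14 | 14 − 5 = 9 days | Definition: 0 of those days |
| B. As A, but leaves on day 4 | 14 − 4 = 10 days | Definition: 0 of those days |
| C. Leaves on day 5, dies outside hospital on day 10 | 9 days, plus any failure-free days before discharge | Death rule: 0 in total |
| D. Leaves on day 5, readmitted to the index site with recurrent failure on day 9 | 9 days | Readmission rule: only the last failure-free period counts |
| E. As D, but readmitted elsewhere | 9 days | No rule applies; the credit stands |

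A and B contradict the definition. C has two possible scores. D is corrected and E is not. In A and B, 14 − d is the most that can be wrongly credited; if failure resolves before day 14, the error is smaller.

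**Step 3: effect on an arm mean.** Per patient: 9/73 = 0.123 days and 10/73 = 0.137 days. For an assumed net excess of five such patients in one arm (5/73 = 6.8%): 5 × 9/73 = 0.616 and 5 × 10/73 = 0.685 days. Against the target: 0.616/2 = 31% and 0.685/2 = 34%.

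**Step 4: other assumed shares.** These assume discharge on day 5, affected patients in one arm only, and a shift that reduces a true 2-day difference. Power is by normal approximation at 66 per group and SD 4.1.

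| Share of one arm | Shift (share × 9) | % of 2 days | Power |
|---|---|---|---|
| 1% | 0.09 | 4.5 | 0.76 |
| 3% | 0.27 | 13.5 | 0.68 |
| 5% | 0.45 | 22.5 | 0.58 |

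At a 5% share, moving discharge from day 10 to day 3 changes the shift from 0.05 × 4 = 0.20 to 0.05 × 11 = 0.55 days, and power from 0.71 to 0.53. If the shift goes the other way, it inflates the difference instead. Equal shares with similar discharge days largely cancel in the mean difference.

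**The case against.** The strongest reply is that the discharge sentence is a default and the sentences after it are its exceptions. Much of that stands, and it rules out several stronger readings that a reader might infer.

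- *That a known death is overridden by discharge.* The death sentence has no limit on place of death, and nothing gives the discharge sentence priority. Death as the exception is the natural reading. What remains is that the order is not written down.
- *That every discharged patient is credited through day 14 whatever follow-up shows.* The readmission sentence contradicts this. What remains is that it covers one route only.
- *That transfers of patients on organ support are scored as successes.* The text speaks only of discharge from the hospital. Transfer and leaving against advice are neither included nor excluded.
- *That each affected patient moves the arm mean by 14/73 = 0.19 days, so that five shift the difference by 0.96 days, 48% of the target.* This needs a full 14-day error. A patient who leaves with organ failure gains only the days after discharge. A full 14-day gap could arise only for a death after discharge scored against the natural reading.
- *That the comparison is biased.* Open-label discharge decisions make an imbalance possible; nothing shows one.

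It may also be said that a journal article condenses a fuller protocol, where discharge destination would be handled. That is fair for transfers. It does not answer the main point, because the article states a rule and that rule gives a value contrary to the definition beside it. The article defers secondary outcomes, subgroups and major deviations to the analysis plan, but not the scoring of the primary endpoint.

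**Conclusion.** The concern holds in a limited form. As written, the discharge rule credits about 14 − d failure-free days to a patient who leaves on day d with SOFA-defined organ failure, against the endpoint's definition, and only readmission to the index site corrects it. Precedence between discharge and death is unstated, though the intended order is fairly clear.

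The size is unknown. The illustration of 0.6 to 0.7 days, 31 to 34% of the target, rests on an assumed net excess of five patients in one arm, discharge on day 4 or 5, and failure that persists to day 14. With 1 to 3% of one arm and discharge on day 5, the shift is 0.09 to 0.27 days. With equal shares it is close to nil. The reason to act is that the primary endpoint should give each patient one score consistent with its definition, and this can be secured cheaply before analysis.

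**What to change.** Reword the primary endpoint in three parts.

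1. State that death before day 14, in or out of hospital, gives OFFD = 0 regardless of discharge, using the vital status already collected for 90-day mortality.
2. Limit the post-discharge credit to patients with no SOFA-defined organ failure and no organ support at discharge.
3. For patients who leave with organ failure or are transferred, use organ status to day 14 where it can be obtained. Where it cannot, do not credit those days automatically as failure-free. Specify their handling before the arms are compared, and vary it in a sensitivity analysis. Counting all such days as failure is one option, but it is a worst-case imputation and departs from the missing-at-random approach in Statistical analysis, so it is better kept as one end of the sensitivity range. Say also how readmission to another hospital is scored.

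The cost is wording and a small case report form item on discharge destination, organ status and organ support at discharge. No extra patients are needed. The drawback is that the item must be completed retrospectively for those already enrolled, 73 of 146 as of December 2024. If the full protocol or analysis plan already contains these conditions, it is enough to align the published definition with them.

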#### Secondary endpoints

Part I: process endpoints

Proportion of patients’ average heart rate recovered to < 95 bpm at different time periods after enrollment (24 h, 48 h, 72 h, and 96 h after enrollment). This assessment was derived from continuous heart rate variability (HRV) monitoring, with meticulous exclusion of factors including sputum suction procedures, patient handling, and other medical interventions that could potentially influence heart rate.HRV within 24 h, 48 h, 72 h, and 96 h after enrollmentChanges in plasma interleukin-6 between day 1 and day 5Changes in plasma C-reactive protein between day 1 and day 5

*Part II: Patient centered endpoints*

In hospital and 90-day mortalityProportion of intensive care unit (ICU) admissionChanges in pancreatitis activity scoring system (PASS) scores from day 1 to day 7 after enrollmentIncidence of bleeding requiring interventionIncidence of gastrointestinal perforation or fistulaIncidence of pancreatic fistulaProportion of patients whose enteral nutrition meets the target nutrient intake on day 7 and day 14New-onset organ failure as judged by SOFA scoreNew-onset mechanical ventilationNew-onset RRTNew-onset vasoactive drug therapyICU free and alive days to day 14Ventilator free and alive days to day 14Vasopressor free and alive days to day 14RRT free and alive days to day 14Requirement of minimally invasive drainageRequirement of open surgeryLength of hospital stayExpense of the index hospitalizationIncidence of infected pancreatic necrosis (IPN)

